## Abstract

**Introduction:**

Paralytic ileus is a frequent and serious complication of severe stroke, associated with poor prognosis and prolonged hospitalization. Current pharmacological options are limited by side effects and uncertain efficacy. Although electroacupuncture has shown promise in improving gastrointestinal motility, high-quality trials specifically targeting stroke-related paralytic ileus are still lacking, leaving an important evidence gap.

**Methods:**

This multicenter randomized controlled trial will recruit at least 100 severe stroke patients with paralytic ileus across China. Participants will be randomly assigned (1:1) to an electroacupuncture or sham electroacupuncture group. The electroacupuncture group will receive standardized electroacupuncture, while the sham electroacupuncture group will undergo sham acupuncture without electrical stimulation. The primary outcome is weekly spontaneous bowel movements. Secondary outcomes include bowel movement regularity, abdominal circumference, bowel sounds, emergency medication use, Glasgow Coma Scale, National Institutes of Health Stroke Scale, Modified Rankin Scale and length of hospitalization. Adverse events will be systematically monitored and recorded throughout the study. Efficacy will be assessed using linear mixed-effects models or generalized linear mixed models, with both intention-to-treat and per-protocol analyses performed.

**Discussion:**

The results of this multicenter RCT will provide robust evidence on the efficacy and safety of electroacupuncture for stroke-related paralytic ileus and may inform future clinical practice and guideline development.

**Clinical trial registration:**

https://itmctr.ccebtcm.org.cn/, identifier ITMCTR2025000003.

## Introduction

1

Stroke ranks as the third leading cause of death and the fourth leading cause of disability-adjusted life-years (DALYs) worldwide (1). Among its complications, gastrointestinal dysfunction, particularly paralytic ileus, is a major concern in severe stroke cases (2, 3). Paralytic ileus, characterized by absent stool passage for three or more consecutive days without mechanical obstruction (4), affects over 40% of severe stroke patients (5, 6) and is commonly mistaken for constipation. In this vulnerable population, factors such as immobility, autonomic dysfunction, and medication side effects predispose to paralytic ileus (7). It contributes to abdominal distension, heightened risks of infection and malnutrition, and impairs neurorecovery by restricting rehabilitation and aggravating inflammation, placing considerable strain on patients and healthcare systems (8, 9).

Despite its clinical importance, paralytic ileus treatment remains conservative—nasogastric decompression, supportive care, and prokinetics (4, 5). Yet decompression poorly restores motility (10). Options like coffee or gum chewing aid recovery (11, 12) but face limitations in stroke patients: coffee may cause agitation; gum chewing is impractical in unconscious cases. Prokinetics, though common, show variable efficacy and risk of dependency or resistance (13–15). These limitations highlight the pressing need for safer and more efficacious therapeutic alternatives.

Electroacupuncture (EA), a type of acupoint stimulation therapy, has demonstrated potential in regulating autonomic function, enhancing gastrointestinal motility, and optimizing neurological outcomes (16, 17). Clinically, EA is proven to enhance postoperative bowel recovery, particularly in abdominal surgery cases, through improved gut motility (18, 19). However, current evidence for acupoint therapy in stroke ileus is weak, hampered by methodological issues such as inappropriate sham acupuncture controls or insufficient blinding (20, 21). Furthermore, severe stroke patients exhibit the highest incidence of paralytic ileus, yet EA’s therapeutic efficacy in this specific population remains largely unexplored.

Given these considerations, we have designed a randomized controlled trial (RCT) to assess the safety and efficacy of EA in alleviating paralytic ileus in patients with severe stroke.

## Methods

2

### Trial design and setting

2.1

This multicenter RCT will be conducted across three clinical centers in Guangdong, China. The study protocol follows the SPIRIT guidelines, and a detailed flowchart of the trial design is provided (Figure 1). The study protocol has been approved by the Medical Ethics Committees of all participating centers.

**Figure 1 fig1:**
[figure not shown]
Study protocol flowchart.

### Patients

2.2

Participants will be recruited from the collaborating centers. Eligible patients will include those diagnosed with paralytic ileus (4) following severe stroke (22). Eligible patients will be screened per protocol.

#### Inclusion criteria

2.2.1

Participants must meet the following criteria to be included in the study:Diagnosis of severe stroke as defined by clinical assessment, with a Glasgow Coma Scale (GCS) score ≤ 12.Clinically confirmed diagnosis of paralytic ileus, with the requirement of enteral nutrition for more than 48 h.Age between 18 and 65 years, regardless of gender.Stable vital signs for at least 24 h, with an Acute Physiology and Chronic Health Evaluation II score < 31.For patients unable to provide informed consent, permission will be obtained from a direct family member before inclusion in the study.

#### Exclusion criteria

2.2.2

Participants will be excluded from the study if they meet any of the following criteria:Contraindications to acupuncture, such as severe dermatological conditions, bleeding disorders, or other contraindications to acupuncture therapy.Severe dysfunction of the heart, liver, or kidneys, significant electrolyte disturbances, or other serious systemic diseases.Pregnant or breastfeeding women.History of severe primary gastrointestinal disorders, including inflammatory bowel disease, irritable bowel syndrome, gastrointestinal bleeding, gastrointestinal perforation, or functional constipation; or a history of major gastrointestinal surgery, such as stoma creation or extensive bowel resection.Continuous agitation or status epilepticus, rendering the patient unable to cooperate with the study or potentially interfering with the study results.Use of laxatives such as lactulose, or prokinetic agents such as neostigmine, prior to enrollment in the trial.

### Randomization and blinding

2.3

Eligible participants will be randomly and equally assigned to the EA group or the sham electroacupuncture (SEA) group using a central web-based randomization system (http://47.119.117.255). The randomization sequence will be generated with a block size of 4. An independent researcher, who is not involved in outcome assessment, will perform the randomization and group allocation.

Since acupuncture involves manual procedures, only the acupuncturists will be unblinded. Outcome assessors, physicians, nurses, caregivers, patients, and statisticians will all remain blinded. An independent monitor will be responsible for maintaining the integrity of the blinding process.

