The primary outcome, WSBM, is a discrete quantitative variable assessed at multiple time points. Depending on the data distribution, either a linear mixed-effects model or a generalized linear mixed model will be used. Secondary outcomes with continuous repeated measures, such as bowel sound frequency, GCS, and the National Institutes of Health Stroke Scale (NIHSS), will be analyzed using linear mixed-effects models if the data are approximately normally distributed. Otherwise, generalized linear mixed models with appropriate distributions will be applied. Rescue medication use, as a count variable assessed over time, will be analyzed using generalized linear mixed models. The Modified Rankin Scale (mRS), being an ordinal variable assessed repeatedly, will be analyzed using ordinal logistic regression models for repeated measures. Length of hospital stay, a continuous variable, will be compared between groups using either the independent samples t-test or the Mann–Whitney U test, depending on distribution. Adverse events, as categorical variables, will be analyzed using the chi-square test or Fisher’s exact test, depending on the expected cell counts. The primary outcome will be analyzed as the sole confirmatory endpoint, while all secondary outcomes will be treated as exploratory. For repeated measures, *post hoc* correction will be applied, but no formal multiplicity adjustment will be conducted across multiple secondary endpoints. Additional statistical analyses are provided in the Supplementary material.

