### Safety evaluation

3.3

All adverse events will be recorded on paper CRFs by the acupuncturist, including the time of occurrence, severity, management, and their relationship to the intervention. Mild adverse events will include minor bleeding, bruising, acupuncture-related pain, and localized infection; serious events will include organ injury and uncontrolled hemorrhage. In the event of serious adverse events, the intervention will be stopped immediately, appropriate treatment will be provided, and the event will be reported to the Institutional Review Board within 24 h.

The timeline for each assessment is detailed in Table 2.

**Table 2 tab2:** Timeline of each assessment.

Outcomes	Intervention			Follow-up	
	Week 0	Week 1	Week 2	Week 4	Week 6
Weekly spontaneous bowel movements		**×**	**×**	**×**	**×**
Bowel movement regularity		**×**	**×**	**×**	**×**
Rescue medication use		**×**	**×**	**×**	**×**
Bowel sounds	**×**	**×**	**×**		
Abdominal circumference	**×**	**×**	**×**		
Glasgow coma scale	**×**	**×**	**×**	**×**	**×**
National institutes of health stroke scale	**×**	**×**	**×**	**×**	**×**
Modified rankin scale	**×**	**×**	**×**	**×**	**×**
Length of hospitalization					×
Safety evaluation					

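### A single published block size of 4, with unblinded acupuncturists at three centres, makes allocation partly deducible if blocks run per centre; varied, undisclosed blocks within centre would be safer (minor)

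*Protocol article*

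**What the plan says.** Under Randomization and blinding (2.3), patients are "randomly and equally assigned to the EA group or the sham electroacupuncture (SEA) group using a central web-based randomization system". The article adds that "The randomization sequence will be generated with a block size of 4", and names no other size. On who allocates, it says "An independent researcher, who is not involved in outcome assessment, will perform the randomization and group allocation". On blinding, "only the acupuncturists will be unblinded"; assessors, physicians, nurses, caregivers, patients and statisticians stay blinded, and an independent monitor oversees this.

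Under Trial design and setting (2.1): "This multicenter RCT will be conducted across three clinical centers in Guangdong, China". Section 2.3 neither states nor rules out stratification by centre.

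Under Statistical analysis (2.8), for the primary outcome, "either a linear mixed-effects model or a generalized linear mixed model will be used", depending on the distribution. No model terms are listed, and "Additional statistical analyses are provided in the Supplementary material". In Table 2 the row "Weekly spontaneous bowel movements" has no Week-0 entry. Bowel sounds, abdominal circumference, GCS, NIHSS and mRS do have one.

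**The concern.** In permuted blocks of known, constant size, the last place or places of a block follow from the places before it. A central system hides the list but cannot prevent that deduction by someone who knows the block size and the earlier assignments. Here the size is in print, and the acupuncturists necessarily learn the arm of each patient they treat. Some exclusion criteria in section 2.2.2 are open-ended, such as contraindications to acupuncture beyond those named and serious systemic disease in general. If a person who can anticipate the next arm has a say in such a judgement or in its timing, enrolment can become selective, and no later analysis reliably repairs that.

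If the blocks run over one list shared by the three centres, prediction from within a centre is hard, but nothing keeps the arms balanced within a centre. Any difference between centres in outcome could then be partly mixed with treatment by chance.

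**Working it through.** **1. The plan's own figure.** Inputs from Sample size (2.7): WSBM 7.11 ± 2.20 against 5.71 ± 1.50, α = 0.05 (two-sided by section 2.8), power 0.90, 20% dropout.
- Difference: 7.11 − 5.71 = 1.40.
- Pooled SD: √((2.20² + 1.50²)/2) = √3.545 = 1.883.
- Power from the noncentral t with unequal variances: 0.899 at 39 per group and 0.906 at 40, so 40 per group is right.
- Dropout: 40/(1 − 0.20) = 50 per group, 100 in total.

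The stated size reproduces without any covariate adjustment.

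**2. Predictability if blocks run per centre.** Input: blocks of 4, two per arm, giving 6 equally likely orders and 24 positions. The observer knows the size and all earlier assignments in that list.

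| Place in block | Chance it is certain | Chance the best guess is right |
|---|---|---|
| 1st | 0 | 1/2 |
| 2nd | 0 | 2/3 |
| 3rd | 1/3 (first two alike) | 1/3 × 1 + 2/3 × 1/2 = 2/3 |
| 4th | 1 | 1 |

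- Certain: (1/3 + 1)/4 = 33.3%, which is 8 of the 24 positions.
- Correct guesses: (1/2 + 2/3 + 2/3 + 1)/4 = 70.8%.
- For comparison, a constant, known block of 6 gives 25.0% certain and 68.3% correct; a block of 8 gives 20.0% and 66.6%.

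**3. One list shared by three centres.** Simulation of 100 patients in 25 blocks of 4, each patient falling at random to a centre. The article gives no centre shares, so I assume a range from equal to 60/25/15.
- Guessing from the running balance at one's own centre is right about 52–53% of the time.
- The average difference between arms within a centre is about 3 to 4 patients.
- The chance that some centre differs by 7 or more is about 35% with equal shares and 28% with 60/25/15. For 8 or more it is 25% and 19%.
- Information on the treatment effect kept after adjusting for centre (the sum over centres of n₁n₀/n, divided by 25) averages 98%, with a 5th percentile of 94%.

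**4. What covariates could add to the primary analysis.** The article gives no R² (share of WSBM variance explained), so 5% to 20% is an assumption. The effective size is 40/(1 − R²) per group.

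| Assumed R² | Effective n per group | Power |
|---|---|---|
| 0 | 40 | 0.907 |
| 0.05 | 42 | 0.920 |
| 0.10 | 44 | 0.933 |
| 0.20 | 50 | 0.956 |

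**The case against.** A reader might infer that the trial has no centre stratification, that the models leave out centre and baseline, and that precision on the primary outcome is therefore wasted. The article does not support this. It is silent on stratification. It names only a class of model and lists no terms at all, not even treatment or time, so an unlisted term is not an excluded one. It points to supplementary material that is not shown, and such details are commonly left to the full protocol or the SAP. WSBM has no Week-0 value to adjust for, the share of its variance explained by centre or by other Week-0 measures is unknown, and the sample size never relied on adjustment.

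A reader might also add the two harms together. They belong to opposite designs: the 71% figure needs per-centre lists, and the imbalance figures need a shared one.

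On predictability, allocation is central and done by an independent researcher, physicians and nurses are blinded, and a monitor guards the blinding. Nothing says that acupuncturists screen or enrol. If several share a centre, each may know only part of the sequence, so 33% and 71% are upper figures for a fully informed observer. On imbalance, chance differences under random allocation are not systematic bias, and the average loss of information is small.

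These arguments lower the severity. They do not answer the stated rule itself: one constant block size, in print, in a trial whose operators know the arm.

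**Conclusion.** The point holds in a narrow form and is minor, something to consider. The constant, published block size is the plan's own statement, and the step from it to 33% certain and 71% guessable is exact, provided that blocks run per centre and someone knows the centre's earlier assignments. Whether such a person can affect enrolment is not documented. With a shared list, prediction is close to chance, and the weakness is a 28–35% chance of a within-centre difference of 7 or more, at an average cost of about 2% of information. Nothing here shows that the stated 90% power is wrong or that the models omit centre or baseline. Any gain in precision on WSBM from covariates is modest: about 1 to 5 percentage points of power under an assumed R² of 5% to 20%.

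**What to change.** 1. State whether blocks run within centre or across one list.
2. Stratify the existing web list by centre, with block sizes that vary at random (for example 4 and 6) and are not disclosed to site staff. If recruitment has begun, do so from the next block. Stratifying gives balance within centres; varying the size means that the position at which a block closes is no longer known. Simply moving to a constant 6 would gain little (25.0% certain, 68.3% guessable).
3. As a low-cost addition, fix before unblinding that the primary model includes centre, and that the models of bowel sounds, abdominal circumference, GCS, NIHSS and mRS include the Week-0 value. If the supplement or SAP already says so, only confirmation is needed.

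The cost is a regenerated list in a system already in use, a sentence in the analysis plan and a few degrees of freedom.

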### Intervention

2.4

Licensed acupuncturists with at least 3 years of experience will administer the interventions. The protocol, grounded in traditional Chinese acupuncture theory and refined through expert consultations, employs Jin’s Three-Needle Therapy. The “Dingshen-zhen,” “Weisan-zhen,” and “Changsan-zhen” acupoint groups are targeted for their effectiveness in gastrointestinal and neurological conditions (Figure 2). See Supplementary material for more details.

**Figure 2 fig2:**
[figure not shown]
Acupoint anatomical locations. A1, Dingshen I; A2, Dingshen II; A3, Dingshen III; B1, Neiguan (PC6); B2, Zhongwan (CV12); B3, Zusanli (ST36); C1, Tianshu (ST25); C2, Guanyuan (CV4); C3, Shangjuxu (ST37).

To ensure patient blinding, both groups will utilize a Patient-Blinded Acupuncture Auxiliary Device, previously validated in our studies for its effectiveness in maintaining blinding integrity (23). The device includes a plastic pedestal and three guide tubes, facilitating vertical, oblique, and horizontal needle insertions (Figure 3). Its design is identical for both groups.

**Figure 3 fig3:**
[figure not shown]
Patient-blinded acupuncture auxiliary device. **(A)** horizontal insertion; **(B)** oblique insertion; **(C)** vertical insertion; **(D)** hollow adhesive patch; **(E)** non-hollow adhesive patch; **(F)** acupuncture auxiliary device; **(G)** hollow instruments for electroacupuncture; **(H)** non-hollow instruments for sham electroacupuncture.

#### EA group

2.4.1

In the EA group, hollow instruments are used to allow sterile needle insertion. Sterile, disposable stainless steel acupuncture needles (Huatuo; 25 × 0.3 mm and 40 × 0.3 mm) with sharp tips will be inserted into predefined acupoints to an appropriate depth. Manual manipulation will be performed to elicit the deqi sensation. Electroacupuncture will then be administered using the Hua Tuo SDZ-II device. Electrodes will be connected from the right ST25 to CV12 and from the left ST25 to CV4, with continuous stimulation at 10 Hz and 0.5–4 mA for 30 min.

#### SEA Group

2.4.2

Participants in the SEA group will receive an identical-appearing intervention to ensure effective blinding. The same patient-blinded auxiliary device will be applied, using non-hollow instruments and blunt-tip needles that do not penetrate the skin. A pricking sensation will be simulated to mimic the tactile experience of real acupuncture.

Electrodes will be placed at the same acupoints as in the EA group. However, no electrical current will be delivered. The procedure is designed to maintain visual and procedural consistency with the EA group while avoiding actual needle insertion or stimulation.

#### Basic treatment

2.4.3

Basic supportive care includes continuous monitoring of vital signs to enable early detection of clinical deterioration. Oxygen therapy is provided as needed to prevent or correct hypoxemia and ensure adequate tissue oxygenation. For patients requiring mechanical ventilation, individualized ventilatory strategies are implemented and regularly adjusted based on respiratory parameters and clinical response. Fluid and electrolyte balance is actively maintained throughout the hospitalization, with adjustments guided by laboratory findings and the patient’s clinical condition. Progressive enteral nutrition support is provided in Supplementary material, along with infection management, glycemic control, and other supportive treatments as clinically indicated.

#### Rescue medication

2.4.4

If a patient has no bowel movement for three or more consecutive days, a glycerin suppository (Glycerin Enema) will be administered rectally to stimulate evacuation (24). If constipation persists for another 3 days after enrollment or during treatment, bowel-regulating medication should be initiated promptly, with dosage and frequency recorded. Bowel movements within 24 h after suppository administration will not be counted as spontaneous.

#### Follow-up

2.4.5

Patients will have video or in-person follow-ups at Weeks 4 (2 weeks after treatment) and 6 (4 weeks after treatment).

### Data management

2.5

Study data will be recorded on case report forms (CRFs) by assessors, with participants identified by randomization numbers. Two independent staff will perform double data entry. The data management system will validate entries for range and logic errors. All data will be encrypted, with access restricted to authorized personnel. Paper CRFs will be securely stored at the South China Research Center for Acupuncture and Moxibustion for no less than three years after the completion of the study.

### Quality control

2.6

The trial will use web-based randomization and standardized training to minimize bias. All data will be entered in real-time via CRFs, with three-tier monitoring of outcomes, documentation, and data management.

### Sample size

2.7

This RCT evaluates Weekly Spontaneous Bowel Movements (WSBM) as the primary outcome, aiming to compare the mean differences between the two groups. The sample size was estimated using PASS 15 software, based on preliminary data from a pilot study (WSBM: 7.11 ± 2.20 in the EA group and 5.71 ± 1.50 in the SEA group). Given a significance level (*α*) of 0.05 and a power (1-*β*) of 0.9, the required sample size per group was determined to be 40 participants. Considering a 20% dropout rate, at least 100 participants will be enrolled. Additional recruitment may be conducted if feasible.

### Statistical analysis

2.8

This study will employ both intention-to-treat analysis and per-protocol analysis. The intention-to-treat analysis will include all randomized participants, while the per-protocol analysis will focus on those with good compliance and no major protocol violations. The safety analysis set will comprise participants who receive at least one intervention and have safety evaluations.

All statistical analyses will be conducted using SAS software (version 9.4; SAS Institute Inc., Cary, NC, USA). Two-sided tests will be used, with *p* < 0.05 considered statistically significant. Continuous variables will be assessed for distribution using histograms and Q–Q plots, and reported as mean ± standard deviation (SD) or median (interquartile range, IQR), as appropriate. Categorical variables will be presented as counts (n) and percentages (%). Between-group comparisons will use independent t-tests or Mann–Whitney U tests for continuous variables, and Chi-square or Fisher’s exact tests for categorical variables.

The primary outcome, WSBM, is a discrete quantitative variable assessed at multiple time points. Depending on the data distribution, either a linear mixed-effects model or a generalized linear mixed model will be used. Secondary outcomes with continuous repeated measures, such as bowel sound frequency, GCS, and the National Institutes of Health Stroke Scale (NIHSS), will be analyzed using linear mixed-effects models if the data are approximately normally distributed. Otherwise, generalized linear mixed models with appropriate distributions will be applied. Rescue medication use, as a count variable assessed over time, will be analyzed using generalized linear mixed models. The Modified Rankin Scale (mRS), being an ordinal variable assessed repeatedly, will be analyzed using ordinal logistic regression models for repeated measures. Length of hospital stay, a continuous variable, will be compared between groups using either the independent samples t-test or the Mann–Whitney U test, depending on distribution. Adverse events, as categorical variables, will be analyzed using the chi-square test or Fisher’s exact test, depending on the expected cell counts. The primary outcome will be analyzed as the sole confirmatory endpoint, while all secondary outcomes will be treated as exploratory. For repeated measures, *post hoc* correction will be applied, but no formal multiplicity adjustment will be conducted across multiple secondary endpoints. Additional statistical analyses are provided in the Supplementary material.

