Clinically, the findings from this trial could substantially influence practice by validating EA as an effective and safe therapeutic option for managing gastrointestinal dysfunction in critically ill stroke patients. If effective, EA may become an integral part of multimodal treatment strategies in intensive care units, thereby enhancing patient recovery, reducing the use of pharmacological laxatives, and improving overall quality of care. Moreover, positive results could support the wider clinical adoption of acupuncture-based interventions, potentially reducing complications related to impaired gut motility, shortening hospitalization, and informing future guideline recommendations for the management of stroke-related paralytic ileus.

This multicenter trial may face challenges in ensuring the consistency of acupuncture procedures across different study sites. First, all acupuncturists will undergo standardized training and obtain certification prior to patient enrollment, with continuous quality control measures implemented throughout the study to ensure procedural fidelity. Although no formal blinding index will be conducted, the use of a validated patient-blinded auxiliary device, together with centralized monitoring, is expected to maintain the integrity of blinding and minimize inter-centre variability. Second, potential adherence issues, particularly in the critical care context, will be addressed through enhanced communication strategies, structured education for healthcare providers, and routine follow-up with patients and their families. Third, for patients with impaired consciousness, a multidimensional outcome assessment system will be adopted to ensure objectivity and reliability in evaluations. Finally, all intercurrent events and instances of missing data will be systematically recorded. Sensitivity and subgroup analyses will be conducted to assess their potential impact on the study outcomes and to ensure the robustness of the results.

In conclusion, this rigorously designed RCT is expected to provide robust evidence for the efficacy and safety of EA in severe stroke-related paralytic ileus, while also offering important translational insights that may inform clinical decision-making and future guideline development.

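### The article promises robust safety evidence, but about 50 patients exposed to EA and an equality test for adverse events cannot supply it for uncommon or serious needle harms

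*Protocol article*

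**What the plan says.** **The promise.** The Discussion part of the Abstract says the results "will provide robust evidence on the efficacy and safety of electroacupuncture for stroke-related paralytic ileus". The last sentence of section 4 (Discussion) repeats it: the trial "is expected to provide robust evidence for the efficacy and safety of EA in severe stroke-related paralytic ileus". Earlier in section 4, in a conditional sentence about what the findings could do for practice, the article speaks of "validating EA as an effective and safe therapeutic option for managing gastrointestinal dysfunction in critically ill stroke patients".

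**The size.** Section 2.7 sizes the trial on weekly spontaneous bowel movements only, at 40 per group, and then says: "Considering a 20% dropout rate, at least 100 participants will be enrolled. Additional recruitment may be conducted if feasible". The Methods part of the Abstract gives the allocation: "Participants will be randomly assigned (1:1) to an electroacupuncture or sham electroacupuncture group".

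**The harms and the comparator.** Section 3.3 lists minor bleeding, bruising, needling pain and local infection as mild events, and says "serious events will include organ injury and uncontrolled hemorrhage". Section 2.4.2 describes the sham as using "blunt-tip needles that do not penetrate the skin", with no current delivered and with a simulated prick.

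**The analysis.** Section 2.8 states: "Adverse events, as categorical variables, will be analyzed using the chi-square test or" Fisher's exact test, the choice depending on expected cell counts. Tests are two-sided at 0.05. The same section reports categorical variables as counts and percentages, defines a safety analysis set, and refers to the Supplementary material for further analyses.

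**The concern.** Safety is one of the two questions the trial says it will answer, and the claim is made for critically ill patients. The stated test asks whether the two arms have equal event rates. For harms that arise from a needle passing through the skin, the sham arm should show almost none by design, so equality is not the question of interest. A reader needs to know how high the rate with EA could be, given what was seen in the patients exposed. Neither a p-value nor a percentage answers that.

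At this sample size the test also cannot flag the events that matter most. If the safety conclusion leaned on it, the article's claim would go further than the data could support for uncommon and serious harms.

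**Working it through.** **Inputs.** From the documents: pilot means and SDs of 7.11 (2.20) and 5.71 (1.50), two-sided alpha 0.05, power 0.90, 20% dropout, at least 100 patients, 1:1 (sections 2.7 and 2.8, Abstract). The article gives no adverse event rates, so every event rate below is an assumption and is shown as a range.

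**1. The plan's own sample size.** Difference 7.11 − 5.71 = 1.40. Pooled SD = √((2.20² + 1.50²)/2) = 1.883. Normal approximation: n = (1.960 + 1.282)² × (2.20² + 1.50²)/1.40² = 38.01, so 39 per group. With a Welch t-test, power is 0.899 at 39 and 0.906 at 40, so 40 per group. Dropout: 40/(1 − 0.20) = 50 per group, 100 in total. The stated figure reproduces. It rests on efficacy alone and gives about 50 patients on EA.

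**2. Which test applies.** With k events on EA and none on sham, the expected count in each event cell is k/2. Under the usual threshold of 5 (assumed; the article names none), Fisher's test applies until k reaches 10.

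**3. Events needed for significance.** With k v 0 events and 50 per arm, the two-sided Fisher p-value is 2 × C(50,k)/C(100,k):

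| EA v sham events | p |
|---|---|
| 4 v 0 | 0.117 |
| 5 v 0 | 0.056 |
| 6 v 0 | 0.027 |

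At least 6 of 50 (12%) against none is required.

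**4. Power against a zero sham rate.** Power = P(X ≥ 6), X ~ Binomial(50, p):

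| Assumed true EA rate | Power |
|---|---|
| 1% or 2% | about 0% |
| 5% | 3.8% |
| 10% | 38% |
| 15% | 78% |
| 20% | 95% |

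**5. What zero events would show.** Exact upper limits for 0 of 50: 1 − 0.05^(1/50) = 5.8% (one-sided 95%) and 1 − 0.025^(1/50) = 7.1% (two-sided 95%). At a true rate of 2%, the chance of seeing no event in 50 is 0.98^50 = 36%.

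**6. Sensitivity to the number exposed.**
- With 40 exposed, zero events allow 7.2% (one-sided) or 8.8% (two-sided).
- With 100 exposed, they allow 3.0% or 3.6%.
- With 100 per arm, Fisher's test still needs six events: 5 v 0 gives p = 0.059 and 6 v 0 gives 0.029.
- One event in 50 would raise the two-sided exact upper limit to 10.6%, so the bound depends on the data.

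**The case against.** **The plan does not equate non-significance with safety.** A reader might infer that a non-significant result will be reported as proof that EA is safe. The article states no such rule, and section 2.8 makes the primary outcome the only confirmatory endpoint. This objection stands.

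**The plan is more than a p-value.** Counts and percentages are to be reported, and section 3.3 records timing, severity, management and relationship to the intervention for all adverse events. Five serious events would be visible as 10% v 0%, and each would go to the review board within 24 hours. This also stands. What is absent is a statement of uncertainty around those percentages. Confidence intervals may be in the Supplementary material, and their absence from an article would not be a point in itself. But no unseen analysis lets about 50 exposed patients give robust evidence on uncommon serious harms, and that claim is made in the article.

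**The sham is not free of every named harm.** A reader might infer that it cannot cause any of them. A simulated prick can hurt and a blunt needle might bruise, while hemorrhage can occur in either arm for reasons unrelated to needling. The near-zero sham rate is therefore argued only for needle-site bleeding, local infection and organ injury.

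**Practice sentence, size and power.** The sentence in section 4 about influencing practice is conditional and is not itself a promise of safety. The firm promises are in the Abstract and the closing sentence of section 4. Fifty per arm is a minimum, and the test works for common effects. Low power for rare harms is usual in a trial of 100, which is a reason to claim less.

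**Conclusion.** The point holds in a limited form. The article promises a strength of safety evidence that the design does not have for uncommon or serious harms, and its only stated adverse event inference does not give the quantity needed. At 50 per arm, fewer than six EA events against none on sham cannot reach significance, and zero events would still leave a true rate of up to 5.8% (one-sided) or 7.1% (two-sided) compatible with the data. For common needle effects of about 15–20% the test is adequate.

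These results assume about 50 patients exposed, a sham rate of zero for harms from skin penetration, and event rates chosen for illustration. More recruitment would tighten the bound without changing the conclusion. The primary analysis, the sample size for efficacy and the efficacy conclusion are not affected.

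**What to change.** **Section 2.8.** Make the main safety summary the per-patient incidence of adverse events in each arm with exact 95% confidence intervals, separately for serious and mild events. For events that can occur in both arms, add a risk difference with its confidence interval. State that a non-significant test is not evidence of safety.

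**Abstract (Discussion) and closing sentence of section 4.** Keep the efficacy wording apart from the safety wording, and describe the latter as preliminary safety data. When results are reported, give the upper confidence limit computed from the observed events and the number actually exposed. Do not fix a figure in advance: the 5.8% and 7.1% limits apply only to zero events in 50.

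**Cost.** A few lines of analysis and a less favourable safety claim. No extra patients or data are needed.
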